#### Needs Identification Tool

To effectively address the needs of veterans with HNHR, we developed a needs identification tool to identify and understand the needs and unmet needs of older adults and improve patient engagement through a peer-led home visit. Peers initially conducted home visits using a longer questionnaire of validated questions to identify needs. The needs identification tool was modified to reflect the peers’ personalized holistic style using conversational language. The peers gather baseline information and identify unmet needs through a series of questions, conversations, and observations in the following domains: mobility, mind, medications, matters most, multicomplexity, and social determinants (Textbox 1). These needs domains were selected based on the 5Ms of geriatrics and previous studies showing that common barriers to patient engagement in outpatient programs include physical symptoms and limitations, mental illness, care fragmentation, isolation and lack of social support, financial insecurity, and poor social and neighborhood conditions [38-41]. These needs were then documented in a study-specific CPRS templated note to harmonize data collection and inform and coordinate care with the PACT regarding the veterans’ needs.

Needs domains.Mobility and functionMobility, past falls, frailty, gait, and balanceActivities of daily living and instrumental activities of daily livingHomebound statusCurrent use of support servicesMindMemoryMood (depression and anxiety)Substance useMedicationsMedication insecurity, refills, questionsMedication adherence concernsMatters mostMeaningful health goalsMulticomplexityChronic medical conditionsChronic disease–related health care needsHearing or vision problemsHealth care useSocial determinantsSocial supportTransportationFood insecurityFinancial stabilityHousing insecurity, housing density, neighborhood safetyLegal concernsTechnology access and ability to use technologyHome safety concerns and needsOutdoor grab barWalkerAssistive devicesBathroom assistive devicesSmoke detectorPresence of clutter, rugs, cords

#### The Passport-2-Wellness

We designed the Passport-2-Wellness educational book with 8 topics that were identified as being most common for, and most relevant to, older veterans with HNHR in the context of the 5Ms of geriatrics (Textbox 2). This Passport-2-Wellness book, which also contains a *Telehealth Visits* section and a section entitled *Healthcare Tools and Notes*, is provided to enrolled veterans as a resource and used by the peers as an educational tool. Peers, in collaboration with the veteran, select relevant topics to review during the intervention.

Passport-2-Wellness educational topics.Mobility and SafetyBarriers to HealthcareIndependent LivingHome Safety ChecklistFalls PreventionCaregiver SupportCaregiver Support TipsCaregiver ResourcesDisaster PlanningWhole HealthIntroduction to Whole HealthYour Personal Health InventorySelf-care and Mind-Body TechniquesAge-Friendly Health System 4MsWhat Is Most Important to You?Memory TipsMood TipsMedication TipsMulticomplexityCommon Chronic Conditions: Diabetes and HypertensionWhat is Diabetes?What Are the Symptoms of Diabetes?How Can You Manage Your Diabetes?Monitoring and Testing Your Blood SugarManaging your Blood SugarWhat My HbA1c MeansHow to Use a GlucometerWhat is HypertensionNutrition and Physical ActivityFood as MedicineWhat Foods to EatWhat Foods to AvoidBenefits of Physical ActivityTips to Increase Physical ActivityWhere Should You Start?Chair YogaCommunity Fitness ZonesHealth CommunicationDoctor Visit Tips and Shared Decision-MakingAdvance DirectivesCare Plan and SMART GoalsCare Plan WorksheetSMART Goals and Progress WorksheetsExtra InformationProblem-SolvingVA Claims, Disability and PensionWomen Veterans Health CareVeteran Decision Aid for Care at Home or in the CommunityCommunity Dental ClinicsTypes of Vascular DiseaseUnderstanding CholesterolChronic Kidney DiseaseCongestive Heart FailureHow You Can Reduce Heart Disease RiskChronic Obstructive Pulmonary Disease (COPD)Understanding Insomnia

#### Peer Training Curriculum

Two hired peers were already certified peer support specialists [25]. There is onboarding training required for national peers in the PACT implementation team at all VA sites for usual peer activities. National peer training incudes competencies in recovery principles, peer support practices, cultural competence, communication, recovery and personal wellness goals, and whole health approaches to services. A complete list of expected knowledge and skill areas can be found in the *Peer Support Specialists Training Manual* [25]. To supplement this training, we developed an educational curriculum for the peers specific to the P2P intervention. This curriculum was developed integrating feedback from PACT providers, peers, key stakeholders, and the home-based primary care team. Overall, the duration of P2P intervention training is 40 hours: 16 hours for educational components and 24 hours for P2P hands-on training. Peer training was provided by multidisciplinary PACT and home-based primary care team members, including geriatricians, social workers, and nurses. Peers also received hands-on training in the use of VA CPRS, conducting chart review, and conducting a remote video visit. Peers made 3 home visits with the home-based primary care team to learn the process for conducting safe home visits, using personal protective equipment (because this intervention started during the COVID-19 pandemic) and checking for home safety and unmet needs. Some of the training was via *Talent Management System*, the VA’s enterprise-wide education, leadership development, learning, and employee development system. Training components are shown in Table 2.

**Table 2 table2:** Peer support specialist Peer-to–Patient-Aligned Care Team (P2P) training curriculum.

Component			Required training			Duration (hours)		Modality
**P2P didactic training**								
	**Veterans with high needs and high risk**							
		Identifying the needs and unmet needs of veterans with high needs and high risk			1		Remote presentation	
		Social determinants of health			2		TMS^a^ course	
	Safety	Personal protective equipment training			1		In-person meeting with local occupational health	
	Mobility and functional limitations	Falls, assistive devices, ADLs^b^, and IADLs^c^			1		Remote presentation	
	Mental health	Managing depression, SUD^d^, and stress			2		In-person meeting with local recovery coordinator and mental health peers for information on VA^e^ resources and hospital tour	
	**VA** **vehicle**							
		Courses for driving a government vehicle			1		TMS course	
		Defensive driving, driving fundamentals, credit card, and so on (varies by facility)			1		TMS course	
	Motivational interviewing	Understanding good communication practices			1		TMS course	
	Social work	Social work services: transportation and long-term support services, VA and community resources, and caregiver resources			2		In-person meeting with local social worker	
	Telehealth	Remote care technology and tablet device use, digital divide consult, and mock remote video visit			2		TMS course	
	Research	VA required training in human participant research and HIPAA^f^			2		TMS course	
**P2P hands-on training**								
	Home visit	HBPC^g^ training and shadowing on home visit safety			12 (3 home visits)		In-person home visits with HBPC team	
	P2P tools	Use of the Passport-2-Wellness, needs data–gathering tools, and mock telephone calls			8		P2P team in person and remotely	
	VA records	Use of CPRS^h^ and chart review training			4		In person with program coordinator	
**Recommended training**								
	**Whole health**							
				Introduction to whole health, health coaching, and goal setting: SMART^i^ goals	2		TMS course	
				“Taking charge of my life and health” facilitator training	25 (5 days)		Remote learning (Zoom; Zoom Video Communications, Inc) and class discussion, partner activities, and small groups	
	Diabetes mellitus overview			About type 2 diabetes, hyperglycemia, hypoglycemia, and complications	2		In-person meeting with local diabetes nurse practitioner	
	Nutrition			Healthy eating, portion sizes, if you drink alcohol, and food shopping tour	4		In-person meeting with local dietician and nurse practitioner	

^a^TMS: Talent Management System.

^b^ADL: activity of daily living.

^c^IADL: instrumental activity of daily living.

^d^SUD: substance use disorder.

^e^VA: Department of Veterans Affairs.

^f^HIPAA: Health Insurance Portability and Accountability Act.

^g^HBPC: home-based primary care.

^h^CPRS: computerized patient record system.

^i^SMART: strategic, measurable, attainable, results-oriented, and time-bound.

### Data Collection

#### Demographic and Clinical Measures

The study team collected demographic, clinical, and use data from the CPRS and GECDAC on age, sex, race and ethnicity, marital status, care assessment need score [34], JEN Frailty Index [35], Nosos score [36,37], service-connected eligibility, 2-year emergency room visits, urgent care visits and primary care visits, and diagnosed conditions and services used among both intervention and comparison group participants (Table 3).

**Table 3 table3:** Data collection.

Outcome measures						Description of measures		Data source		Schedule		
										Baseline		6 months
**Demographic and clinical data**												
		Demographics^a^				Age, sex, race, ethnicity, marital status, and rurality		CPRS^b^ chart review and GECDAC^c^ data pull		✓		N/A^d^
		Clinical characteristics^a^				Dementia, comorbidities, Nosos, CAN^e^, and JFI^f^, service-connected eligibility, and 2-year emergency room and urgent care		GECDAC data pull		✓		N/A
		Frailty				Fatigue, resistance, ambulation, illness, and loss of weight		Morley 5-item FRAIL^g^ scale [42]		✓		N/A
		Homebound status				Difficulty leaving the house and frequency of veteran leaving the house		NHATS^h^ homebound status questionnaire [38]		✓		N/A
**Aim 1: to test the preliminary effect of the intervention on patient engagement through PACT^i^ health care use**												
	Patient engagement: Health care use and support services use^a^				Primary care PACT encounters, consults, and support services (eg, homemaker and home health aide)		CPRS chart review and GECDAC data pull		✓		✓	
**Aim 2: to identify the number and types of needs and unmet needs as well as needs addressed using the P2P^j^ needs identification tool**												
	**Needs identification**											
			Health needs			ADLs^k^, IADLs^l^, and help needed; mobility needs; hearing, vision, and memory problems; and medication refills and adherence		Katz ADL Index [43], Lawton IADL Scale [44], and study-specific questions		✓		N/A
			Social needs			Food insecurity, housing insecurity, transportation, social isolation and loneliness, legal concerns, and technology needs		Two-item food insecurity screen [45], VA homeless screener [46], PRAPARE^m^ survey [47], UCLA^n^ Loneliness Scale [48], P2P legal concerns project-specific 1-item question, and VA digital divide consult		✓		N/A
			Home safety needs			Home safety devices need (eg, grab bars and bathroom assistive devices) and safety concerns (eg, unsafe steps and dark or poor lighting)		P2P project-specific checklist		✓		N/A
**Aim 3: to evaluate the feasibility and acceptability of the P2P intervention**												
	**Process evaluation**											
			Feasibility and acceptability			Quantitative: number of unique veterans referred and enrolled, average number of visits per veteran, average total number of consults placed per veteran, and average total number of GEC^o^ services received		CPRS chart review and GECDAC data pull		✓		✓
			Facilitators, barriers, improvements, and satisfaction			Qualitative: study-specific questions and semistructured interviews of veterans, PACT providers, peers, and leaders		P2P study-specific questionnaires, semistructured interviews, and periodic reflections		✓		✓

^a^Data collected for both intervention and comparison groups.

^b^CPRS: computerized patient record system.

^c^GECDAC: Geriatric and Extended Care Data Analysis Center.

^d^N/A: not applicable.

^e^CAN: care assessment need.

^f^JFI: JEN Frailty Index.

^g^FRAIL: fatigue, resistance, ambulation, illnesses, and loss of weight.

^h^NHATS: National Health and Aging Trends Study.

^i^PACT: patient-aligned care team.

^j^P2P: peer-to–patient-aligned care team.

^k^ADL: activity of daily living.

^l^IADL: instrumental activity of daily living.

^m^PRAPARE: Protocol for Responding to & Assessing Patients’ Assets, Risks & Experiences.

^n^UCLA: University of California Los Angeles.

^o^GEC: Geriatric and Extended Care.

#### Primary and Secondary Outcome Measures

Our primary outcome was patient engagement, defined as the number of outpatient PACT encounters. We obtained these data from the GECDAC and from CPRS chart reviews for both intervention and comparison groups. Patient engagement is a broad concept that combines positive patient behavior, such as obtaining preventive care, with patient activation [49]. In this study, we measured veteran engagement with the VA health care system by measuring participation in outpatient care and services. Peers collected data on frailty [42], homebound status [38], health needs, needs related to social determinants of health, and home safety needs. Secondary descriptive outcomes among intervention participants included prevalence and types of needs and unmet needs, actions taken to assist with meeting needs, and use of health care services, specifically services in the home (Table 3).

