A promising approach to address these gaps at the VA concerns the use of peer support specialists (peers) [21-24]. Peers are veterans hired by the VA to help other veterans, usually those with serious mental illnesses, to engage them in their treatment successfully [25]. Peers are required to be veterans and must complete peer certification training. Peer certification training is conducted by a single contractor hired by the VA mental health services office. The training is at no cost to peers. Expected competencies include recovery principles, peer support practices, cultural competence, whole health approach to services, and advocacy. Continued education is required of all peers, including a minimum of 15 hours of competency-related training every year [25]. Peers promote recovery by using their common bond of being veterans and sharing their own recovery stories, providing encouragement, instilling a sense of hope, and teaching coping, empowerment, and social skills to veterans [25]. Peers understand the social and historical experiences shaping the veterans and connect with veterans in a different manner than the rest of their health care team. Being veterans themselves, peers are in a unique position to connect with veterans and assist with navigating the VA. Patient-aligned care teams (PACTs) at the VA are comprehensive medical homes that use a multidisciplinary team-based approach to effectively provide primary care and manage chronic conditions [26,27]. Preliminary studies suggest that embedded peers in mental health and primary care PACTs encourage veterans to be more active in managing their health [21-24,28-30]. Peers serve as role models, community connectors, and health care navigators. The preliminary success of the original peer support programs in specialty mental health led to congressional support for the creation of a peers-in-the-PACT program as part of the Maintaining Internal Systems and Strengthening Integrated Outside Networks (MISSION) Act of 2018 (section 506) with the implementation of peers at 30 VA sites [31]. Peers are relatively new members of the VA primary care PACT teams, and sites are working out the roles for peers in primary care.

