### Matched Comparison Group

Veterans in the matched comparison group were identified from the HNHR list, similar to the method used to enroll veterans into the P2P intervention. Comparison group veterans did not receive any peer services before or during the study period as evidenced by CPRS chart reviews and use data provided by the GECDAC. Comparison group participants were matched with P2P intervention participants on age, care assessment need score [34], JEN Frailty Index [35], and Nosos score [36,37] from the HNHR list for the period during which the P2P participant was recruited. Veterans in the comparison group received care as usual.

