#### Care Coordination, Health Care System Navigation, and Linking to Resources in Collaboration With the PACT

The peers document the identified needs and a narrative of their observations in a templated CPRS note and add primary care PACT team members as cosigners. Peers collaborate with the appropriate PACT team member (primary care physician, nurse case manager, social worker, or pharmacist) to coordinate the ordering of needed consults and services. Care coordination to address unmet needs is discussed during team huddles (limited during the COVID-19 pandemic), via telephone calls or Microsoft Teams messaging, or in person.

Examples of unmet needs and linking to resources in collaboration with the PACT may include reaching out to the social work department for transportation concerns, linkage to food banks and meals on wheels for food insecurity concerns, or homemaker and home health aide for self-care concerns; reaching out to pharmacy for medication concerns; or working with the PACT nurse case manager or physician to refer veterans with falls or safety concerns to the falls clinic or order physical therapy, home safety assessment, or prosthetics for needed home safety durable medical equipment.

Peers may increase veteran health care engagement by bridging veterans back to their primary care team. Peers help veterans to navigate the health care system (eg, schedule appointments, send reminders, and provide guidance through the health care system bureaucracy) and provide emotional and social support (eg, identify VA and local social resources programs such as food banks and tenant advocacy). They continue to communicate with the veterans on the progress of their care plan and follow up on the status of the identified unmet needs (eg, resolved or not resolved) and assist with unresolved unmet needs by following up on referrals, consults, and orders.

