### Peer Assessment

Peers work with the veterans to ensure that they receive the needed services to enable them to remain in the community and address care fragmentation across providers and services. The P2P intervention is designed to be 6 months in duration, including 1 home visit during month 1 and contacts once every 2 weeks thereafter. The peers assess whether further follow-up is needed, past the 6 months, to continue advocating for the veteran or whether the veteran could be discharged from the P2P intervention. Peers complete a P2P discharge summary indicating the reason for the discharge (eg, veteran does not require any additional peer support, or veteran has stopped communication with peer, or voluntarily withdrawn) and a summary of participation in the program.

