#### Quantitative Analysis

For our primary outcome, we will first calculate the difference in the number of primary care PACT outpatient encounters 6 months before and after enrollment for each participant in both intervention and comparison groups. An independent, 2-tailed, 2-sample *t* test will then be used to compare the means of the pre-post differences in the number of outpatient PACT encounters between intervention and comparison groups. The mean pre-post difference will be reported for each group with the corresponding SDs and 95% CIs. The folded F statistics will be evaluated to report either the pooled or Satterthwaite *P* value. We will calculate group-specific means and proportions for sociodemographic and clinical factors. At baseline, categorical variables will be compared between groups with the Pearson chi-square test or with the Fisher exact test for rare outcomes. The *t* test will be used to compare means across groups. *P* values will be reported, with lower values interpreted as more stable and less likely to be sporadic. All quantitative analyses will be performed using SAS 9.4 (SAS Institute Inc).

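### The primary outcome does not separate peer contacts from PACT clinician encounters, so on one plain reading delivery of P2P counts as its effect

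*Protocol article*

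**What the plan says.** Primary and Secondary Outcome Measures gives the endpoint: "Our primary outcome was patient engagement, defined as the number of outpatient PACT encounters". The source is stated next: "We obtained these data from the GECDAC and from CPRS chart reviews for both intervention and comparison groups". Quantitative Analysis makes the analysis variable "the difference in the number of primary care PACT outpatient encounters 6 months before and after enrollment for each participant" and compares its mean between groups with a t test described as "An independent, 2-tailed, 2-sample". Neither section mentions encounters with peers.

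On who the peers are, the article points two ways.

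- **Inside the PACT.** Background: "Peers are relatively new members of the VA primary care PACT teams". The Conclusions place them in the primary care service, and the Discussion (Overview) treats P2P visits as routine clinical work.
- **Outside the PACT.** Table 1 has peers and the PACT conferring as two parties. In the Care Coordination section peers write the CPRS note and PACT staff are asked to cosign it, and its list of PACT members whom peers approach (physician, nurse case manager, social worker, pharmacist) contains no peer. Remote Care has peers presenting the veteran to a PACT provider. P2P Interventionists says that the peers were hired and paid through the mental health services office.

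Peer Assessment describes a 6-month intervention "including 1 home visit during month 1 and contacts once every 2 weeks thereafter". Table 1 has peers complete follow-up notes in CPRS. Matched Comparison Group says: "Comparison group veterans did not receive any peer services before or during the study period".

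**The concern.** Aim 1 asks whether P2P raises veterans' engagement in care, measured by PACT outpatient use. The Care Coordination section gives the mechanism: peers reconnect veterans with their primary care team. The outcome should therefore capture contact with that team.

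If a peer's own visits and calls enter the count, the intervention adds to its outcome simply by being delivered. The error runs one way, because comparison veterans have no peer contacts in either window. Neither the pre-post difference nor the matching removes it. A positive result could then mean only that the peers kept to their schedule.

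**Working it through.** **1. The plan's own figures.** 38 + 76 = 114; 38/114 = 33.3%, 76/114 = 66.7%, 76/38 = 2. The stated sample and 1:2 ratio reproduce. The article gives no SD, target effect or significance level, and it says that the sample size did not come from a power calculation.

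**2. Scheduled peer contacts in the 6 months after enrollment.**
- Table 1 (home visit in week 3, fortnightly meetings in months 2-5), at two per month: 1 + 4 × 2 = 9.
- The same by calendar weeks: 1 + (4 × 52/12)/2 = 1 + 8.67 = 9.7.
- Peer Assessment, if contacts run to the end of month 6: 1 + (5 × 52/12)/2 = 1 + 10.83 = 11.8.

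This gives about 9 to 12 per intervention veteran if fully delivered. The comparison group has 0 by selection.

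**3. Effect on the estimate.** Let *k* be the mean number of P2P peer contacts per intervention veteran that are coded as PACT encounters. These contacts occur only after enrollment and only in the intervention group, so the difference in mean change shifts upward by *k*. This holds whatever the SD or significance level.

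**4. Effect on the test.** Assumptions: two-sided level 0.05; common SD of the change of 5 encounters, range 3 to 8; no true effect on clinician encounters.

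SE = SD × √(1/38 + 1/76) = 0.1987 × SD, that is 0.596, 0.993 and 1.589 at SD 3, 5 and 8. The noncentrality is *k*/SE with 112 degrees of freedom and critical value 1.981. For *k* = 2 and SD 5 it is 2/0.993 = 2.01. The noncentral t distribution gives the probability of P<.05:

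| Contacts counted per veteran (*k*) | SD 3 | SD 5 | SD 8 |
|---|---|---|---|
| 0 | 5% | 5% | 5% |
| 1 | 38% | 17% | 10% |
| 2 | 91% | 51% | 24% |
| 3 | >99% | 85% | 46% |
| 5 | >99% | >99% | 88% |

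**5. Scale.** Two contacts are about one fifth of the schedule (2/9.7 = 21%), so partial coding is enough to matter. With *k* = 0 the rate stays at the nominal 5%.

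**The case against.** The strongest reply is that peers are not PACT members for this purpose. The Background sentence is a general remark on staffing, whereas the sections describing the intervention mostly treat the PACT as the team to which peers link veterans. On that reading a PACT encounter already means one with a clinician. In addition, the process measures under Aim 3 include visits per veteran, which may be where peer contacts are recorded. A CPRS note is not shown to be a counted encounter, and clinic or provider codes are the kind of detail that an article leaves to a fuller document.

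Much of this stands. A reader might infer that the article defines peers as PACT members, that peer contacts were in fact counted, or that Aim 1 cannot be answered. The documents support none of these: the wording points both ways, and the coding is not shown. The number of contacts delivered may also fall below schedule, since the Discussion describes a more flexible schedule and Peer Assessment allows for veterans who withdraw or stop communicating.

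What does not stand is that the matter is only operational detail. The stated endpoint has two plain readings, and one of them includes the intervention's own delivery. Recording visits under Aim 3 does not remove them from the Aim 1 count.

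**Conclusion.** The concern holds as an ambiguity in the sole primary outcome with a possible bias in one direction. It is not a demonstrated bias. If peer contacts are coded as PACT encounters, the estimated effect is inflated by the mean number counted, up to about 9 to 12 per veteran under full delivery. Two counted contacts would give P<.05 with no true effect about 51% of the time at SD 5 (91% at SD 3, 24% at SD 8).

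The SD, the 5% level and the number of contacts counted are assumptions. The article says only that lower P values will be read as more stable, so the shift in the estimate matters more here than the rejection rate. If peer contacts are not counted, there is no bias from this source, and one clarifying sentence settles the point.

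**What to change.** - Define the primary count as outpatient encounters in which a PACT clinician (for example physician, nurse, social worker or pharmacist) took part.
- Exclude peer-only contacts in both groups and in both 6-month windows.
- Keep encounters in which a peer telepresents the veteran to a PACT clinician. A filter that drops every encounter involving a peer would delete real clinician contacts.
- Report peer contacts under Aim 3 as delivery of the intervention.
- Give the all-encounter count as a labelled sensitivity analysis.

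The cost is a sentence in the outcome definition and a small amount of filtering of data from sources already in use. The observed effect may be smaller. The Results section says that analysis is underway, so the rule should be fixed and dated before group results are compared or, if they have already been seen, reported as a later clarification.
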